# Effect of electroacupuncture on opioid consumption in patients with chronic musculoskeletal pain: protocol of a randomised controlled trial

**DOI:** 10.1186/1745-6215-13-169

**Published:** 2012-09-17

**Keywords:** Acupuncture, Chronic pain, Electroacupuncture, Opioid medication, Pain education, Randomised controlled trial

## Abstract

**Background:**

Chronic musculoskeletal pain is common and has been increasingly managed by opioid medications, of which the long-term efficacy is unknown. Furthermore, there is evidence that long-term use of opioids is associated with reduced pain control, declining physical function and quality of life, and could hinder the goals of integrated pain management. Electroacupuncture (EA) has been shown to be effective in reducing postoperative opioid consumption. Limited evidence suggests that acupuncture could assist patients with chronic pain to reduce their requirements for opioids.

The proposed research aims to assess if EA is an effective adjunct therapy to standard pain and medication management in reducing opioids use by patients with chronic musculoskeletal pain.

**Methods:**

In this multicentre, randomised, sham-acupuncture controlled, three-arm clinical trial, 316 patients regularly taking opioids for pain control and meeting the defined selection criteria will be recruited from pain management centres and clinics of primary care providers in Victoria, Australia. After a four-week run-in period, the participants are randomly assigned to one of three treatment groups to receive EA, sham EA or no-EA with a ratio of 2:1:1. All participants receive routine pain medication management delivered and supervised by the trial medical doctors. Twelve sessions of semi-structured EA or sham EA treatment are delivered over 10 weeks. Upon completion of the acupuncture treatment period, there is a 12-week follow-up. In total, participants are involved in the trial for 26 weeks. Outcome measures of opioid and non-opioid medication consumption, pain scores and opioid-related adverse events are documented throughout the study. Quality of life, depression, function, and attitude to pain medications are also assessed.

**Discussion:**

This randomised controlled trial will determine whether EA is of significant clinical value in assisting the management of debilitating chronic pain by reducing opioids consumption and their associated adverse events, as well as improving the quality of life for those with chronic pain. Such an outcome will provide the rationale for including EA into multidisciplinary programmes for effective management of chronic musculoskeletal pain.

**Trial registration:**

Australian New Zealand Clinical Trial Registry (ACTRN12609000676213)

http://www.anzctr.org.au/trial_view.aspx?ID=308008

## Background

### Opioid medications for chronic pain

One in five Australians suffers from chronic pain, with the majority having chronic musculoskeletal pain (CMP) [1]. Chronic pain is the third most costly health condition and costs the Australian government $4.7 billion dollars each year [2].

Due to the difficulty in managing CMP, morphine and other strong opioids have been increasingly used. Opioid medication (OM) prescriptions for CMP doubled from 8% to 16% in the United States of America between 1980 and 2000 [3]. In Australia, 13% of chronic pain patients were on some type of opioids in a 1999 survey [4]. From 1999 to 2005, the total OM consumption in Australia had increased by more than eight times for oxycodone (to 38.9 mg per capita), 40 times for hydromorphone and five times for fentanyl [5].

The effectiveness of OM for CMP is debatable [6]. Three recent systematic reviews concluded that OM reduced pain by 30% in the short term. However, its long-term efficacy is unknown [7-9]. A follow-up study of patients who were still on OM 10 years after completion of a multidisciplinary pain management programme reported that those patients had poorer quality of life, were more depressed, and adopted passive strategies for pain management, indicating that opioids were ineffective for this group [10]. Furthermore, opioids are associated with a high rate of adverse events (AEs), such as drowsiness, nausea, vomiting, constipation, dry mouth, dose escalation and/or tolerance, hyperalgesia and dependence when used for treating chronic pain [11].

Part of integrated pain management is to assist patients in reducing OM use through pain medication management (PMM), including education about pain and adjustment of pain medication, and is usually given by clinicians and nurses. However, there are very few other options. There is an urgent need to identify a therapy that could effectively assist the reduction of OM.

### Electroacupuncture

Acupuncture, one of several non-pharmacological therapies for managing pain, has been found to stimulate the releases of endogenous opioid peptides in animals and humans [12-14]. A recent human study using positron emission tomography found that patients with fibromyalgia displayed reduced binding potential of opioids in comparison to pain-free controls [15]. In addition, nine sessions of acupuncture increased opioid binding potential in certain brain regions of a similar group of patients significantly more than sham acupuncture [16]. Combined with the increased release of endogenous opioid peptides upon acupuncture, this increased binding effect might in turn enhance the efficiency of OM and decrease the amount required for functional improvement and pain relief.

When used in postoperative pain, electroacupuncture (EA) - acupuncture combined with electrical stimulation - reduced the use of postoperative morphine by more than 60% and was 30% better than sham procedures. It also reduced the severity and incidence of OM-related side effects [17,18]. Our pilot study in 35 patients with chronic pain also showed that EA reduced OM consumption by 39% in comparison with a 25% reduction in the sham EA group, with 90% patient satisfaction [19].

### Aims

In this multicentre, randomised, sham-acupuncture controlled, three-arm clinical trial, we will evaluate the effect of EA as an adjunct therapy to PMM on OM consumption by patients with CMP. The primary hypothesis is that EA reduces OM consumption significantly more than sham EA. The secondary hypotheses are that:

1. the proportion of participants who experience 50% or more OM reduction is significantly higher in the EA group than that in the sham EA group;

2. EA reduces OM-related AEs significantly more than sham EA;

3. EA combined with PMM is significantly better than PMM alone in reducing OM usage and AEs;

4. EA reduces the intensity of pain and improves function significantly better than sham EA;

5. participants having a strong self-reliant attitude to pain consume significantly less OM than those relying on medications for pain relief.

## Methods

The trial is being conducted between July 2009 and December 2012, and has been approved by the Human Research Ethics Committees of Melbourne Health (2009.033), Alfred Health (80.09) and the RMIT University (06/09) to be conducted at the Pain Services of the Royal Melbourne Hospital, the Caulfield Pain Management and Research Centre of the Caulfield Hospital, the Sunshine Hospital, and various sites in Melbourne and Geelong. It has been registered with the Australian New Zealand Clinical Trial Registry (ACTRN12609000676213).

The design of the trial follows the CONSORT statement [20] and the Initiative on Methods, Measurements, and Pain Assessment in Clinical Trial for chronic pain [21]. The procedure of the trial is presented in Figure 1.

**Figure 1 F1:**
[figure not shown]
A flow chart of the trial process.

### Power and sample size calculation

Using sample means from baseline and the end of the treatment phase of the OM consumption data from our pilot study [19], we estimate that a total sample size of 316 will provide 80% power using a 1% level of significance to detect an effect size estimate of 0.48 between the EA and sham EA groups. Because intention-to-treat analysis will be used, no additional participants are required. We plan to recruit 316 participants in total. A dropout rate of 20% is considered to be within the normal range.

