### Randomisation and blinding procedures

After a four-week run-in period, participants who meet all selection criteria are randomly allocated into one of the three groups, namely EA, sham EA or no-EA with a 2:1:1 ratio. An automated telephone randomisation service provided by the National Health and Medical Research Council Clinical Trial Centre at the University of Sydney is used. Before the commencement of the first acupuncture session, the treating acupuncturist dials a toll-free number and enters the identification codes of the trial, the acupuncturist and the site, and the baseline OM weekly dose (morphine equivalent). The participant is then randomly allocated to one of the three groups according to a computer-generated randomisation sequence. The acupuncturist records the allocation in a secure and separate file. The computer-generated randomisation uses stratified permuted blocks to ensure that an equal ratio of participants in EA and sham EA groups in each centre is assigned to each acupuncturist; and to ensure that an equal number of participants consuming high or low dose of OM is assigned to each group. The cut-off OM dose for high or low consumption is 560 mg (morphine equivalents) per week, decided upon by pain specialists on the team based on our pilot study and other published studies reporting average OM consumption by patients with chronic pain [22,23]. Three quarters of the participants are in either the EA or sham EA group and are blinded; one quarter of the participants are in the no-EA group and are be blinded. The success of blinding of the two acupuncture groups is assessed. Details are presented in Assessment of efficacy below.

The acupuncturists and MDs are not involved in outcome assessments. Blinded assessors are required to conduct outcome assessments, collect Medication and Pain Diaries, and check any missing data. The trial data are entered by research assistants and analysed by a statistician. Except for the acupuncturists, all of the above will be are blinded to participant allocation. Professional statistical assistance is also sought to double check the data analysis.

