### Statistical analysis of the trial outcomes

The Statistical Program for Social Science (SPSS, the latest version) is used for data analyses. Baseline categorical data, demographic characteristics such as gender and age category, and numerical data are analysed with *χ*^2^ tests and one-way analysis of variance, respectively, to determine comparability of the three groups on these variables.

Linear mixed models (for continuous outcome variables) and generalised estimating equations (for categorical outcome variables) are used to examine the changes over time in weekly dosage of OM, numbers and types of OM-related AEs, severity of pain and Beck Depression Inventory. *χ*^2^ tests are also used to detect group differences in the numbers of dropouts and AEs.

Both intention-to-treat and per protocol analyses are used. Data from participants who do not violate the treatment protocols will be included in the per protocol analysis. Missing data are dealt with using the last value carried forward method. Missing Beck Depression Inventory and SF-36 data are dealt with according to the relevant manual.

Apart from the effects of types of intervention, the influence on the outcomes of differences between centres and therapists is also analysed. The relationship between OM reduction and attitude to pain are explored.

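### Intention-to-treat analysis does not remove the need for a dropout allowance: the stated 80% power holds only with complete week-14 data and is about 70% at 20% loss

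*Protocol article*

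**What the plan says.** All the design inputs but one stand in the protocol article under Power and sample size calculation. The section states that "a total sample size of 316 will provide 80% power". The test is set at the 1% level, and the aim is "to detect an effect size estimate of 0.48 between the EA and sham EA groups". It derives the effect size from pilot means at baseline and at the end of treatment. It then says "Because intention-to-treat analysis will be used, no additional participants are required", followed by "We plan to recruit 316 participants in total" and "A dropout rate of 20% is considered to be within the normal range".

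The remaining input is the allocation, given under Randomisation and blinding procedures: "namely EA, sham EA or no-EA with a 2:1:1 ratio".

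Three other sections determine what happens when a participant is lost. Withdrawal and Electroacupuncture interventions set to missing the data of participants who withdraw and of those who complete fewer than half of the sessions. Statistical analysis of the trial outcomes adds: "Missing data are dealt with using the last value carried forward method". That section also names linear mixed models for weekly opioid dosage.

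**The concern.** The section treats intention-to-treat as a substitute for a dropout allowance. It is a rule about the analysis set and does not recover an end-of-treatment opioid dose that was not recorded. Something must stand in for that dose. If nothing does, the sample shrinks. If an earlier value is carried forward, the row count is kept, but the value may hold only part of the difference between EA and sham EA. The primary outcome is the change from baseline to the end of treatment, and the planned opioid reduction is spread over weeks 8, 11 and 14. A value carried from an early departure would therefore usually predate most of that reduction.

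At stake is how the primary EA-versus-sham comparison is read. A null result judged against a stated 80% power would be taken as stronger evidence of no effect than the trial can give. At about 70% power, a true effect of 0.48 is missed about 30% of the time, not 20%.

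**Working it through.** **Inputs.** Total 316, power 80%, level 1%, effect size 0.48 and dropout 20% come from Power and sample size calculation; the 2:1:1 ratio comes from Randomisation and blinding procedures. Assumed: a two-sided test (sidedness is not stated), 0.48 as a standardised mean difference with SD 1, a t-test at one time point, and equal dropout in the two arms.

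**Step 1. Reproduce the plan's figure.** Normal approximation with two EA participants per sham participant:

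n(sham) = (2.576 + 0.842)² × (1 + 1/2) / 0.48² = 11.68 × 1.5 / 0.2304 = 76.0, rounded up to 77

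The three-arm total is 4 × 77 = 308. With the noncentral t distribution the smallest total is 312 (156:78 gives 80.5%; 154:77 gives 79.9%). The planned 316 splits as 158 EA, 79 sham, 79 no-EA:

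SE = √(1/158 + 1/79) = 0.1378; noncentrality = 0.48 / 0.1378 = 3.48; critical t (235 df) = 2.597; power = 81.1%

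So 316 is correct for complete data, with only 4 to 8 participants to spare across three arms. A one-sided 1% test needs 264, which does not match 316; this is why two-sided is assumed. A 20% allowance would have given 316 / 0.8 = 395, so none is built in.

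**Step 2. Dropouts contribute no outcome.** 0.8 × 158 ≈ 126 and 0.8 × 79 ≈ 63:

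SE = √(1/126 + 1/63) = 0.1543; noncentrality = 0.48 / 0.1543 = 3.11; power = 69.4%

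**Step 3. All 237 kept, last value carried forward.** If the 20% who drop out hold a fraction f of the effect, and the SD is unchanged, the mean contrast becomes 0.48 × (0.8 + 0.2f). The effect detectable with 80% power at 158:79 is 0.474, so the full-follow-up effect needed is 0.474 / (0.8 + 0.2f).

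| Scenario at 20% dropout | Analysed | Effect tested | Power | Full-follow-up effect for 80% power |
|---|---|---|---|---|
| No loss (reference) | 158:79 | 0.480 | 81.1% | 0.47 |
| No outcome from dropouts | 126:63 | 0.480 | 69.4% | 0.53 |
| Carried forward, f = 3/4 | 158:79 | 0.456 | 76.1% | 0.50 |
| Carried forward, f = 1/2 | 158:79 | 0.432 | 70.4% | 0.53 |
| Carried forward, f = 0 | 158:79 | 0.384 | 57.6% | 0.59 |

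**Step 4. Smaller loss.** At 10% loss with no outcome from dropouts, 142:71 gives 75.8%, so the stated 80% fails well before 20%.

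**The case against.** A reader might infer that the trial's real power is 58 to 70%. The documents do not support that as a statement of fact, for these reasons:

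- The article calls 20% dropout within the normal range. That can be read as a tolerance and is not necessarily a forecast. It is, however, the only dropout figure given.
- 58% assumes that no dropout holds any treatment contrast. Opioid use is recorded daily through weeks 5 to 14, so late departures would hold part of any effect. 58% is a lower bound within these scenarios.
- 70% is not a ceiling. Power is 76% if three quarters of the effect is carried, and approaches 81% as f approaches 1.
- The 126:63 case is not the planned analysis, which keeps everyone and carries values forward.
- The article plans mixed models on weekly dosage. Repeated measures could raise power by an amount that depends on a within-person correlation the article does not give.
- If the pilot estimate of 0.48 already included dropouts, some dilution is inside it and the shortfall is smaller. The article does not say.

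All of this stands against quoting a single range as the truth. None of it rescues the stated reason: the section relies on intention-to-treat, not on a mixed model or a pre-diluted effect size. Reading the test as one-sided does not remove the problem either. Power would then be 78% for completers only and 67% under full dilution, and that reading does not reproduce 316.

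It is also fair that the sum itself is right. The defect lies in the justification and in the unconditional power statement, and correcting it changes neither conduct nor analysis.

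**Conclusion.** The sentence is wrong as written, and the 80% power claim holds only if week-14 opioid data are complete. At 20% dropout, power for the primary comparison is about 70% in the two middle scenarios: 69% with no outcome from dropouts and 70% with half the effect carried. It is about 76% if three quarters is carried and 58% at the lower bound.

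The figures rest on a two-sided 1% test, an unchanged SD, equal dropout in both arms, a single-time-point t-test, and a 0.48 not already diluted by pilot dropout. That 316 leaves almost no reserve needs fewer assumptions: it follows from the article's own inputs once the test is taken as two-sided.

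**What to change.** Delete the sentence that intention-to-treat makes an allowance unnecessary and keep 316. Replace it with a statement on these lines:

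*With 316 randomised (158 EA, 79 sham EA), the trial has 80% power for an effect size of 0.48 at the two-sided 1% level only if week-14 opioid data are complete. At 20% loss, power is about 70%, and possibly as low as 58%, depending on how much of the treatment effect the carried-forward values hold. The effect detectable with 80% power is then about 0.53 if dropouts contribute no outcome, and about 0.50, 0.53 or 0.59 if carried values hold three quarters, half or none of the effect.*

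List the assumptions beside it, confirm the sidedness of the test, and say whether the pilot's 0.48 was computed with dropouts included. Give each detectable effect with its own scenario: a single 0.53 set against a range that reaches 58% would be wrong at the low end, where about 0.59 is needed.

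The cost is one rewritten paragraph and a less favourable power statement. Enrolment, design and analysis do not change.

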### Participant recruitment

Patients attending three major pain management centres are notified of the trial by leaflets displayed at the centres or referred by the staff at the pain clinics. Information about the trial is also disseminated through health professionals’ networks, including Chinese medicine, chiropractic, general practice, massage therapy, naturopathy, osteopathy, pharmacy and physiotherapy and through networks for patients with chronic pain, such as Chronic Pain Australia. Interested patients complete a form to express their intention to participate. A researcher from the trial administration centre (RMIT University) then conducts an initial screening, which is followed by a face-to-face interview with a researcher and assessment by a medical doctor (MD) at one of the hospital sites prior to randomisation.

#### *Inclusion criteria*

Participants meeting the following criteria are included:

1. age between 18 and 85 years at entry

2. confident in conversational and reading English

3. suffering from CMP, regardless of the locations of pain

4. have taken OM regularly for more than two months without dose limitation.

#### *Exclusion criteria*

Participants having one or more of the following criteria are excluded:

1. active abuse of OM as judged by an MD

2. severely depressed with suicidal tendency as judged by MDs

3. unstable heart condition, pregnancy or intent to become pregnant, breastfeeding women, epilepsy, brain tumour, current cancer, haemophilia or wearing cardiac pacemakers

4. no general practitioner available for liaison

5. acupuncture treatment in the last 12 months

6. unwilling to reduce OM.

Prior to the eligibility assessment, all participants are provided with adequate information about the study, written in plain English, and all questions are answered to their level of satisfaction before informed consent is signed.

### Randomisation and blinding procedures

After a four-week run-in period, participants who meet all selection criteria are randomly allocated into one of the three groups, namely EA, sham EA or no-EA with a 2:1:1 ratio. An automated telephone randomisation service provided by the National Health and Medical Research Council Clinical Trial Centre at the University of Sydney is used. Before the commencement of the first acupuncture session, the treating acupuncturist dials a toll-free number and enters the identification codes of the trial, the acupuncturist and the site, and the baseline OM weekly dose (morphine equivalent). The participant is then randomly allocated to one of the three groups according to a computer-generated randomisation sequence. The acupuncturist records the allocation in a secure and separate file. The computer-generated randomisation uses stratified permuted blocks to ensure that an equal ratio of participants in EA and sham EA groups in each centre is assigned to each acupuncturist; and to ensure that an equal number of participants consuming high or low dose of OM is assigned to each group. The cut-off OM dose for high or low consumption is 560 mg (morphine equivalents) per week, decided upon by pain specialists on the team based on our pilot study and other published studies reporting average OM consumption by patients with chronic pain [22,23]. Three quarters of the participants are in either the EA or sham EA group and are blinded; one quarter of the participants are in the no-EA group and are be blinded. The success of blinding of the two acupuncture groups is assessed. Details are presented in Assessment of efficacy below.

The acupuncturists and MDs are not involved in outcome assessments. Blinded assessors are required to conduct outcome assessments, collect Medication and Pain Diaries, and check any missing data. The trial data are entered by research assistants and analysed by a statistician. Except for the acupuncturists, all of the above will be are blinded to participant allocation. Professional statistical assistance is also sought to double check the data analysis.

### Trial procedure

As shown in Figure 1, during the initial visit participants provide personal and demographic details and pain history. A four-week run-in period (first to fourth week) follows. During this time, the general practitioners of the participants are notified. Their assistance in prescribing OM and not introducing non-essential therapy during the trial is sought. Participants are also seen by MDs to confirm eligibility. All participants receive PMM, which is provided by MDs in the fifth week. Participants then receive EA, sham EA or no-EA for 10 weeks. Those who are allocated to the no-EA PMM alone group are given the opportunity to have EA treatment at the end of the 10-week treatment period. Participants in the EA and sham EA groups are followed-up for three months.

